##### Adherence to chronic disease treatment

Three measures will assess adherence to HIV and diabetes treatment, respectively. The AIDS Clinical Trials Group (ACTG) adherence questionnaire assesses patients’ current medications, dosing schedule, and medication doses missed over the past four days [50]. The Visual Analog Scale (VAS) assesses general levels of adherence over a 30-day timeframe [51]. For the ACTG and VAS, adherence levels will be examined as continuous variables and dichotomised using standard cut-off scores for adherence (e.g. > = 90%). The third measure is the CASE Adherence Index [52]. Questions on barriers to adherence are also included.

##### Health-related quality of life (HrQoL)

The EuroQol 5 (EQ-5D) will assess HrQoL. The EQ-5D generates a single index that measures how much someone’s life could be extended and improved [53]. From this index, quality-adjusted life years (QALY) will be estimated.

#### Possible mediators and moderators of outcomes

We will collect information on a variety of variables thought to potentially mediate or moderate response to the counselling intervention. The 25-item Social Problem-Solving Inventory Revised-Short Form will be used to assess problem-solving styles. This has been adapted for use among South African populations [54]. The MOS Social Support survey will assess nature and extent of social support [55]. We will also use the 10-item Generalized Self-efficacy Scale to assess participants’ confidence in their ability to solve and cope with a range of problems [56] and the Trauma History Questionnaire will examine lifetime trauma exposure [57]. We will assess other risk behaviours that may impact on study outcomes. We will examine frequency, quantity and chronicity of tobacco use. In addition, the 11-item Drug Use Disorders Identification Test will assess harmful patterns of illicit drug use and dependence [58]. The 10-item Kessler psychological distress scale will examine extent of psychological distress [59].

#### Economic/costing measures

Full economic costs will be assessed from a societal (i.e. provider and patient) perspective within each of the three study arms. For the provider perspective, costs include the costs of the dedicated/designated approach, the costs of chronic disease (HIV/diabetes) care, and the costs of a range of referral services (e.g. referral for TB treatment or inpatient care). While TAU does not include any counselling costs, our inclusion of chronic disease and referral costs for each of the three arms ensures that any potential changes to a broader range of costs is captured. Provider costs will be estimated using a combination of ingredients and step-down methods. A time and motion study will capture the time spent by dedicated or designated CHWs on their daily activities. This will enable an assessment of excess capacity (hypothesized to occur in the dedicated CHWs) and economies of scope (hypothesized to occur in the designated CHWs). Ultimately, a provider cost per patient year will be computed for each study arm/chronic disease.

In the patient perspective, costs include travel costs, the opportunity costs of travel and waiting times, productivity gains or losses and out-of-pocket payments (such as food purchased during a clinic visit, user fees for a private hospital stay, and the costs of additional over-the-counter medicines). Using patient questionnaires, these data will be collected for all of the health services utilized by the patient during the month preceding the interview for the baseline and follow-up assessments (including additional mental health services). We will extrapolate these data in order to calculate a patient cost per patient year for each study arm/chronic disease. In addition, we will collect a range of socioeconomic and demographic data to enable an assessment of patient costs and catastrophic expenditure by socioeconomic status.

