### Patient recruitment and study procedures

Eligible patients will be at least 18 years of age, take antiretroviral therapy (ART) for HIV or medication for diabetes, screen for hazardous/harmful alcohol use (Alcohol Use Disorders Identification Test (AUDIT) score ≥ 8) or depression (Center for Epidemiology Scale on Depression (CES-D) score ≥ 16), not be currently receiving treatment for a mental health condition, and not be participating in another study.

During the study period, all patients presenting for HIV or diabetes care will be asked about their use of alcohol in the past year and recent low mood by their health care provider. Patients who respond positively to one of these two questions will be referred to an assessor for study eligibility screening. After explaining the purpose of the study, the assessor will request verbal consent to screen the patient for possible study inclusion. If a patient is eligible and interested in participating, the assessor will make an appointment for the enrolment visit. At this visit, the assessor will re-screen the participant for study eligibility prior to obtaining informed consent to participate in the trial. Thereafter the assessor will administer the baseline assessment in either English, Afrikaans or isiXhosa, the three official languages of the Western Cape province. This computer-assisted personal interview collects socio-demographic information as well as information on HIV disease, adherence and treatment; diabetes disease, adherence and treatment; CMDs; patterns of health service use and associated patient costs; self-efficacy; readiness to change; problem-solving styles; social support and HrQoL (see Fig. 2 for a description of the measures). Next, a registered nurse will draw up to 10 ml of venous blood to assess the participants’ HIV viral load and HbA1c levels, as appropriate. The blood samples will be sent to a local accredited laboratory for analysis. The assessor will then schedule counselling appointments for participants recruited from facilities assigned to the intervention arms. Ideally, the first session will take place within 3 days of the enrolment visit, with the remaining two sessions scheduled 5 days apart. Participants will have 6 weeks from enrolment to complete these three sessions.

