**Fig. 2 Fig2:**
[figure not shown]
Standard Protocol Items: Recommendations for Clinical Trials (SPIRIT) Figure: schedule of enrolment, interventions and data collection

Irrespective of study arm, all participants will be asked to return to the facility at 6 and 12 months’ post-enrolment to complete a follow-up assessment. During these follow-up visits, the assessor will re-administer the baseline assessment and the nurse will draw blood samples for repeated HIV viral load and HbA1c testing (see Fig. 2). Participants will have 30 days from their scheduled appointment to complete these follow-up assessments before timing out of that particular appointment. Transport costs associated with attending study or counselling appointments will be reimbursed. Participants will receive grocery vouchers for completing the baseline and follow-up assessments.

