#### Interventions: “Dedicated” and “Designated” arms

Participants recruited from facilities in the dedicated and the designated arms will receive three sessions of MI-PST counselling and be referred for further mental health treatment, if needed. Each session is about 60 minutes in duration. In addition, participants will be offered a telephonic booster session 8 weeks after study enrolment. Previous studies have shown that three to four sessions of MI-PST are feasible to implement in PHC settings, acceptable to CHWs and service users, (with attendance declining after three sessions), and impact positively on mental health outcomes [31–33]. The underlying theory and content of this structured counselling approach, and evidence of its efficacy for reducing hazardous/harmful alcohol use and symptoms of depression have been described previously [31–34]. The goals of MI-PST are to motivate participants to change their risk behaviours and to improve their problem-solving skills so they cope better with stress and life problems that are risk factors for CMDs and poor adherence to chronic disease treatment [13–15]. During the sessions, the counsellor and the participant collaborate to identify problems within the participant’s life, and explore one or more of these problems while the counsellor teaches the participant a structured PST approach to resolving these problems. Each session functions iteratively to build readiness to change and problem-solving skills. All sessions have a motivational component, an education component (in which participants are taught problem-solving skills and how to apply them), and includes opportunities to apply newly learned skills through exercises and take home activities. More specifically, participants are taught steps for addressing problems that are important and can be solved; strategies for dealing with negative and intrusive worries that are unimportant; and steps for coping with problems that are important but cannot be solved. These activities are contained in a patient handbook that also summarises the content of the sessions.

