#### Cost-effectiveness analysis

Decision analytical models will be developed to assess intervention costs and outcomes per patient year, from the societal, provider and patient perspective. Discounting will be considered when appropriate. Incremental cost-effectiveness ratios will be used to compare the relative differences between TAU and each active arm. From the provider perspective and within each arm, the cost per patient year will be the product of the utilization of different service units (for example counselling sessions or hospital services) and the unit cost per service. This approach enables uncertainty to be assessed using probabilistic sensitivity analysis on utilization elements and caters for the inherently skewed nature of cost data. From the patient perspective, data collected during patient assessments at baseline and each follow-up will be analyzed using previously established methods [65]. While cost-effectiveness ratios will be computed for each primary outcome measure, QALY measures will allow cost-effectiveness results to be compared with alternative interventions and for allocative efficiency to be assessed.

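### No recall window for patient costs contains the counselling sessions, so as written the active arms' incremental cost against TAU is understated in the patient and societal perspectives

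*Protocol article*

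**What the plan says.** The Trial objectives and Economic/costing measures sections of the protocol article commit to a societal perspective, made up of provider and patient costs.

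- **Patient cost items** (Economic/costing measures): "costs include travel costs, the opportunity costs of travel and waiting times, productivity gains or losses and out-of-pocket payments".
- **Recall period** (same section): services "utilized by the patient during the month preceding the interview for the baseline and follow-up assessments (including additional mental health services").
- **Annualisation** (same section): "We will extrapolate these data in order to calculate a patient cost per patient year for each study arm/chronic disease".
- **Data used in the analysis** (Cost-effectiveness analysis): "data collected during patient assessments at baseline and each follow-up will be analyzed using previously established methods". This section forms incremental ratios for each active arm against TAU.
- **Timing of the sessions** (Patient recruitment and study procedures): they are scheduled at the end of the enrolment visit, after the baseline interview. "Participants will have 6 weeks from enrolment to complete these three sessions".
- **Booster** (Interventions, section on the Dedicated and Designated arms): "participants will be offered a telephonic booster session 8 weeks after study enrolment".
- **Transport** (paragraph on follow-up after Fig. 2): "Transport costs associated with attending study or counselling appointments will be reimbursed".

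The provider side does cost the counselling. It includes the cost of each approach and names counselling sessions as a service unit to be multiplied by a unit cost.

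**The concern.** The intervention creates its own patient burden: three visits of about 60 minutes each, offered in both active arms and not in TAU. A one-month recall suits routine care that continues through the year. It does not suit a short block of visits right after enrolment that is over well before the first follow-up window opens. Extrapolating months in which no session can occur cannot bring the sessions back.

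The article names no other source of patient-side cost. The time and motion tool records how the community health workers spend their day. Multiplying utilisation by unit cost is described for the provider perspective only. The protocol includes chronic disease and referral costs in every arm so that wider cost changes are captured, yet the patient cost of the intervention's own visits has no route into the total. The ratios that decision-makers would read as societal would then rest on too small a cost difference from TAU.

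**Working it through.** The document states no cost figure to reproduce. The check is calendar arithmetic, followed by the direction of the effect.

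**Inputs.** Recall of one month before each interview (Economic/costing measures). Interviews at enrolment, 6 and 12 months, with up to 30 days' allowance at follow-up, and sessions within 6 weeks of enrolment (Patient recruitment and study procedures). Booster by telephone at 8 weeks and sessions of about 60 minutes (section on the Dedicated and Designated arms). Eight clinics per arm with 25 HIV and 25 diabetes participants each (Sample size considerations). One month is taken as 30.44 days.

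**Step 1: the windows.** A window runs from (interview day - 30.44) to the interview day. Sessions occupy days 0 to 6 × 7 = 42; the booster is at day 8 × 7 = 56.

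| Interview | Window (days) | Overlap with days 0-42 | Overlap with days 0-56 |
|---|---|---|---|
| Baseline | -30 to 0 | 0 | 0 |
| 6 months, on time | 152 to 183 | 0 | 0 |
| 6 months, 30 days late | 182 to 213 | 0 | 0 |
| 12 months, on time | 335 to 365 | 0 | 0 |
| 12 months, 30 days late | 365 to 395 | 0 | 0 |

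The first follow-up window opens 5 × 30.44 - 42 ≈ 110 days after the last permitted session and 5 × 30.44 - 56 ≈ 96 days after the booster. Late interviews widen the gap.

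**Step 2: extrapolation.** The two follow-up windows cover 2/12 = 17% of the post-enrolment year. Counselling visits in them number zero, and zero times any scaling factor is zero.

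**Step 3: what is left out.** With full attendance:

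- Visits: 3 per participant, or 8 × 50 × 3 = 1,200 per active arm, against 0 in TAU.
- Session time: 3 × 1 h = 3 h per participant.
- Total time: 3 × (1 + t) hours per participant, where t is travel plus waiting per visit. The document gives no value for t. If t is assumed to lie between 0.5 and 4 h, the result is 3 × 1.5 = 4.5 h to 3 × 5 = 15 h per participant. Over 400 participants, that is 1,800 to 6,000 h per arm.

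These are hours, not money; the document has no unit value to convert them.

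**Step 4: direction.** Let K be the missed patient cost of counselling per active-arm participant. Let R_A and R_T be early patient-side referral costs that the extrapolation also misses, in an active arm and in TAU. Then

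true cost difference - recorded cost difference = K + R_A - R_T.

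K is positive whenever any session is attended. Every TAU participant receives a referral, while active-arm participants are referred if needed, so R_T may exceed R_A and offset part of K. The document gives no figure for any of the three terms.

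**The case against.** The best reply is that the article is a condensed account. It says only that the data will be extrapolated and analysed by established methods from a cited source, within decision models. A fuller economic plan could already multiply attended sessions by a per-visit patient cost, and the proposed fix uses largely the same data. This stands to the extent that nobody can say from the article that the cost will be entered as zero. It does not remove the point. The article does fix the recall month, the data source and the extrapolation, and those three together cannot contain the sessions.

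The objection also holds against several stronger readings that a reader might infer:

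- **That counselling is never costed, or that every ratio is biased.** The provider side costs it. Provider-perspective ratios contain no patient costs and are unaffected.
- **That missed visits run to week 8.** In-person sessions end by week 6; the booster is a telephone call without travel or waiting.
- **That fares are a lost patient cost.** Transport to counselling is reimbursed, so a zero out-of-pocket fare is right in the patient perspective. It matters only as a societal cost, and the article does not say whether reimbursements enter the programme costs.
- **That the gap is a known share of patient cost.** Setting three sessions against an assumed 6 to 12 routine visits a year gives 3/12 = 25% to 3/6 = 50%. The document gives no visit frequency. That ratio also assumes full attendance, equal cost per visit despite reimbursed fares, and no session combined with a routine visit.
- **That the dedicated-versus-designated comparison is biased.** This needs attendance or waiting to differ between the active arms, for which the document gives no evidence. The incremental ratios it names are against TAU.

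**Conclusion.** The point holds for patient costs. As written, the patient-side cost of the three sessions lies outside every recall window in both active arms, with an overlap of 0 days and a gap of about 110 days. The incremental cost against TAU is therefore understated in the patient and societal perspectives. This rests on the recall month, session deadline and interview dates being applied as stated, and on there being no further source of patient-cost data.

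The monetary size cannot be computed. What the document supports is up to 3 visits and about 3 hours of session time per participant, plus travel and waiting of unknown length. Missed early referral use, TAU's included, may offset part of the understatement, so its net size is unknown.

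**What to change.** Add a one-off patient cost of counselling for each active-arm participant and do not annualise it:

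sessions attended × (the participant's own per-visit travel and waiting values from the questionnaire + the value of session time).

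Session counts are already needed for the provider costing, and the baseline interview already collects patient costs of service use. For participants who report no clinic visit in the recall month, a clinic average could be used. Alternatively, put travel, waiting, session time and lost earnings on the counselling session form.

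Value reimbursed transport once in the societal perspective, and check that it is not already counted in programme costs. State as a limitation that early referral use falls outside the windows in all arms.

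The cost is slightly higher stated costs in the active arms and a little more analysis work, or a few extra form items. Randomisation, outcomes and the visit schedule do not change.

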### Sample size considerations

This trial is powered to detect reductions in hazardous/harmful alcohol use and risk of depression at 12-month follow-up. The total sample size required to assess these outcomes is 1200 participants. Sample size calculations are based on a cluster randomised design with two active arms and a control arm. The sample size is based on separate analyses of diabetes and HIV clinic populations, showing a difference between the active arms using two-sided tests at α = 0.05 and 90% power. The statistical comparison will be the mean scores of the CES-D and AUDIT at 12-month follow-up. Guided by international and local cluster trials of depression and alcohol use among primary care patients which found ICCs ranging between 0.025 and 0.040 [60, 61], we set the intra-class correlation at 0.030, which is reasonable for outcomes in patients from PHC facilities. Given findings from previous MI [62, 63] and MI-PST [34] interventions, we expect to find a three-unit difference in AUDIT scores at follow-up between the active arms (considered clinically significant) and a between-person standard deviation of 6.5. For this specification with 20 patients per cluster, eight clinics per arm are needed (24 in total). Guided by findings of PST interventions for depression [34, 64], we anticipate a five=unit difference in CES-D scores between the active arms (considered clinically significant) and a between-person standard deviation of 10 units. For this specification, with 20 participants per cluster, seven clinics per arm are needed (21 in total). We will inflate the cluster size of 20 participants to 25 participants per cluster to cater for a worst-case scenario of a 20% attrition rate. Consequently, a sample size of eight clinics per arm (24 HIV and 24 diabetes services in total), with a cluster size of 25 participants (600 unique participants from HIV and 600 unique participants from diabetes clinics) will meet the inference requirements of the trial. During our pilot phase, we recruited participants with depression and those with hazardous/harmful alcohol use in a 2:1 ratio. To ensure we have sufficient power to detect change in alcohol outcomes during the trial phase, we will examine the number of recruited participants who are eligible based on their alcohol use once we have completed recruitment in each site. If necessary, we will augment the sample by recruiting additional participants with hazardous/harmful alcohol use until the required number of 25 is obtained.

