Despite this evidence, uncertainty about how to configure services and resources within the PHC system to allow for the effective integration of mental health counselling has hindered the implementation of integrated mental health and chronic disease services [25, 38]. On one hand, some have shown that basic mental health counselling can be effectively task-shifted to CHWs already working in PHC settings [29, 39, 40], suggesting that resources available in the PHC system can be reconfigured to enable the delivery of new programmes. In contrast, others have argued that CHWs already in the PHC system are overburdened with multiple tasks and therefore unlikely to prioritise the provision of mental health counselling (and may lack the skills and training to be effective), noting that additional human resources are needed for effective integration of mental health and chronic disease services [41–43]. However, health care systems are unlikely to finance additional resources without evidence of the cost-effectiveness of this investment relative to other approaches to service integration [44]. To the best of our knowledge, there has been no research comparing the relative effectiveness and cost-effectiveness of these approaches [29]. Addressing this knowledge gap is critical for guiding decision-making around how to proceed with integrating mental health into chronic disease care within South Africa’s PHC system.

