Therefore, it is intended that participants in both intervention arms will receive the same counselling programme, but that the job scope of the person delivering the counselling will differ. In facilities assigned to the dedicated arm, one CHW will be added to each facility (eight in total). This CHW will be tasked with providing the counselling programme to patients with HIV and those with diabetes, but will have no other formal chronic disease-related duties. If they have spare capacity, they may assist with administrative and other tasks for the chronic disease care team, but their priority will be the delivery of project MIND’s mental health counselling package. Although these CHWs will be employed as part of the study, their salaries and conditions of employment will match those of the CHWs in the designated arm. In the designated arm, we will identify eight CHW (one per facility) already employed as facility-based counsellors who will be designated to provide the counselling programme to patients with HIV and those with diabetes in addition to their usual chronic disease-related counselling responsibilities. Both dedicated and designated CHWs will be required to complete a time and motion tool that captures their activities and the time spent on each activity on a daily basis. Activities may include mental health counselling, administrative tasks, participation in supervision or training, and other chronic disease activities, which they will be required to specify. This will allow for an exact understanding of their daily activities to be developed.

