
### Data analysis

#### Primary analyses

With 24 clusters, individual-level analyses of trial outcomes are possible. Mixed-effect linear regression models will be used with clusters and participants specified as random effects to take account of the clustering at the facility level and the repeated measures within participants. We will create separate models for alcohol and depression. The analysis will be intention-to-treat. For cluster RCTs, the dropout of clusters is rare. We will consider using multiple imputations to account for missing responses of participants at follow-up in order to reflect the true overall uncertainty of the estimated effect sizes. The two primary outcomes will be ascertained at three time points for each participant. This repeated measure feature will be used to estimate the intervention effects and 95% confidence intervals for the two primary outcomes at 12 months for three contrasts (the contrast between the Dedicated arm and TAU arm, the contrast between the Designated arm and TAU, and the contrast between the two active arms (Dedicated versus Designated), which will serve as the main comparison). Our primary analysis of outcomes will include adjustment for stratification variables. No adjustment for multiplicity will be made since the trial outcome will be determined by the overall significance of the group (intervention) effect. A similar approach will be adopted to estimate the intervention effects and 95% confidence intervals for the secondary outcomes.

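### The 90% power for Dedicated versus Designated treats differences drawn from trials of the counselling itself as expected between two arms that share it, and it carries no correction for 8 clinics per arm

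*Protocol article*

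**What the plan says.** All places are in the protocol article.

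- *Primary analyses* names the contrast that matters most: "the contrast between the two active arms (Dedicated versus Designated), which will serve as the main comparison".
- *Sample size considerations* powers the trial for that contrast, separately in the HIV and diabetes populations: "showing a difference between the active arms using two-sided tests at α = 0.05 and 90% power". For alcohol, "we expect to find a three-unit difference in AUDIT scores at follow-up between the active arms (considered clinically significant", with a standard deviation of 6.5. For depression, "we anticipate a five=unit difference in CES-D scores between the active arms", with a standard deviation of 10. The first value is attributed to findings of earlier MI and MI-PST interventions, the second to findings of PST interventions.
- On clustering, "we set the intra-class correlation at 0.030", from a cited range of 0.025 to 0.040. For AUDIT, "For this specification with 20 patients per cluster, eight clinics per arm are needed (24 in total"; for CES-D the figure is seven clinics per arm. Clusters are enlarged from 20 to 25 to absorb 20% attrition.
- *Interventions: "Dedicated" and "Designated" arms* states that "it is intended that participants in both intervention arms will receive the same counselling programme"; what differs is the job scope of the person delivering it.
- *Background*: "To the best of our knowledge, there has been no research comparing the relative effectiveness and cost-effectiveness of these approaches".

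**The concern.** Two things do not fit together.

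First, the size of the difference comes from a different question. Trials of MI, MI-PST or PST inform what the counselling does. The main comparison asks what changes when the same counselling is given by a worker with a different job scope. By the protocol's own account nobody has studied that, so no earlier trial can supply an expected value for it. The sample size text nevertheless presents 3 and 5 units as what the investigators think they will see.

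Second, the comparison is between two groups of eight clinics. Reference distributions for so few clusters have heavier tails than the normal, and a calculation that ignores this gives too few clinics or too much power.

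At stake is how the main result is read. The trial is meant to guide whether health services pay for an added worker. If the power statement is taken at face value, a non-significant main contrast could be read as showing that the two models work equally well.

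**Working it through.** **Inputs** (all from *Sample size considerations*): two-sided α 0.05; power 90%; ICC ρ = 0.030; m = 20 analysed per cluster; AUDIT Δ = 3, SD = 6.5; CES-D Δ = 5, SD = 10; k = 8 or 7 clinics per arm.

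**Step 1. Reproduce the stated clinics.** n per arm = 2(1.960 + 1.2816)²SD²/Δ²; design effect = 1 + (20 − 1) × 0.03 = 1.57; k = n × 1.57/20.

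- AUDIT: n = 2 × 10.508 × 42.25/9 = 98.65; k = 98.65 × 1.57/20 = 7.74, so 8.
- CES-D: n = 2 × 10.508 × 100/25 = 84.06; k = 84.06 × 1.57/20 = 6.60, so 7.

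Both stated figures come out, so the arithmetic is right for its inputs when normal quantiles are used. The protocol does not name its quantiles; this is inferred.

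**Step 2. Normal-theory power.** SE = SD × √(2 × 1.57/(20k)).

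- AUDIT, k = 8: SE = 0.911; 3/0.911 − 1.960 = 1.335; power 90.9%.
- CES-D, k = 7: SE = 1.498; 5/1.498 − 1.960 = 1.379; power 91.6%. With k = 8: SE = 1.401; power 94.6%.

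**Step 3. Facility-level t.** Power is taken from the noncentral t with noncentrality Δ/SE. Three choices of degrees of freedom were used: 2(k − 1), the two arms alone; 3k − 4, three arms plus a stratum term; and 3(k − 1), three arms. For k = 8 these are 14, 20 and 21; for k = 7 they are 12, 17 and 18.

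| Setting | Normal | t, lowest to highest df |
|---|---|---|
| AUDIT, k = 8, m = 20, ICC 0.03 | 90.9% | 86.5% to 88.1% |
| AUDIT, k = 8, m = 20, ICC 0.04 | 87.5% | 82.5% to 84.3% |
| AUDIT, k = 8, m = 25, ICC 0.03 | 94.1% | 90.5% to 91.8% |
| CES-D, k = 7, m = 20, ICC 0.03 | 91.6% | 86.5% to 88.4% |
| CES-D, k = 8, m = 20, ICC 0.03 | 94.6% | 91.2% to 92.5% |

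Under each df choice, 90% power needs 9 clinics per arm for AUDIT and 8 for CES-D. Adding one cluster per arm as a simple correction gives the same (8.74 and 7.60, rounded up).

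**Step 4. Difference detectable with 90% power, k = 8, ICC 0.03.** With normal quantiles: 3.2416 × 0.911 = 2.95 AUDIT units and 3.2416 × 1.401 = 4.54 CES-D units. With t on 20 df: about 3.1 and 4.8. If HIV and diabetes patients were pooled at 40 per facility with the same ICC (an assumption), t on 20 df gives about 2.6 and 4.0.

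**Step 5. Smaller true differences.** These are illustrations; no document supplies them. With t on 20 df and m = 20, power is 35% at 1.5 AUDIT units and 40% at 2.5 CES-D units. Pooled at 40 per facility, it is 47% and 53%.

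**The case against.** The strongest reply is that both differences are labelled clinically significant. Powering for the smallest difference worth detecting is legitimate even when no earlier comparison exists. That stands, and it is why 3 and 5 units need not change. It does not rescue the wording, which states an expectation and cites trials of the counselling as its basis.

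A second reply is that the t correction is small. It costs AUDIT about 2 to 3.5 points below 90%, and only at the worst-case 20 completers; with all 25 retained at ICC 0.03, AUDIT exceeds 90%. At that ICC CES-D stays above 90% at the 8 clinics actually used, so its seven-clinic figure does not drive the design. The repeated-measures model may also recover power. If baseline and follow-up scores correlated at 0.3 to 0.5 with the ICC unchanged (an assumption), AUDIT power at 20 per cluster would be about 89–94% on 14 df and 91–95% on 20 df. All of this stands, but the power statement takes no credit for repeated measures and gives no correlation.

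Three stronger readings are tempting, and the documents do not support them.

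- A reader might infer that a 3-unit gap would require the designated model to have almost no effect. That needs the size of the counselling effect against control, which the protocol does not give. The *Background* itself reports the argument that existing workers are overburdened and may be ineffective, so a weak designated arm is a possibility it raises.
- A reader might infer that the 90% properly belongs to each active arm against TAU. The cited trials' comparators cannot be seen, and TAU here is supplemented with a resource guide and a referral.
- A reader might infer that the main contrast will probably be non-significant. That depends on a true difference well below target, which nothing here establishes. Low power at half the target is also true of any trial powered at 90%.

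**Conclusion.** The point holds in a limited form. The 3- and 5-unit differences are defensible as targets for Dedicated versus Designated but have no support as expected differences, because the evidence cited concerns the counselling that both arms share.

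The stated 90% is also slightly too high for AUDIT as the calculation is set out: about 86.5–88% with 8 clinics, 20 completers per cluster and ICC 0.03, and 82.5–84% at the top of the protocol's ICC range. For CES-D, seven clinics would give about 86.5–88%, but the eight used give 91–92.5%. These figures rest on the protocol's SDs and ICC, equal cluster sizes, facility-level degrees of freedom of 14 to 21 at eight clinics, and no gain from repeated measures.

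The design is not shown to be inadequate. The defect lies in how the power is justified and stated, and in what a non-significant main contrast could then be taken to mean. The protocol does not claim equivalence from such a result and already plans 95% confidence intervals, but it does not say how the main one will be read.

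**What to change.** In *Sample size considerations*:

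1. Relabel 3 AUDIT and 5 CES-D units as target differences for Dedicated versus Designated, and remove the statement that they are expected on the strength of earlier counselling trials. Do not move them to the TAU contrasts unless the comparators in those trials are shown to match.
2. Restate power with 8 clinics per arm and facility-level t quantiles: about 87–88% for AUDIT and 91–92% for CES-D at 20 completers and ICC 0.03, with the AUDIT figure at ICC 0.040 alongside. If credit is taken for repeated measures, state the assumed correlation.
3. Give the t-based differences detectable with 90% power: about 3.1 AUDIT and 4.8 CES-D units per disease, or about 2.6 and 4.0 if the two populations are pooled.
4. Show power at smaller differences, labelled as assumptions, for example 35% at 1.5 AUDIT units and 40% at 2.5 CES-D units (20 df).

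In *Primary analyses*, add that the 95% confidence interval for the main contrast will be read against 3 and 5 units, so that a non-significant result is not taken as equivalence.

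The cost is rewording and restated figures, with no added clinics or patients. The downside is a slightly less favourable AUDIT power figure.
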